### Inclusion criteria are

- Diagnosis of MFS according to Ghent criteria

- Age ≥ 18 years

### Exclusion criteria

- More than one vascular prosthesis

- Aortic root diameter > 50 mm

- Aortic dissection

- Renal dysfunction (creatinine > 130 μg/ml and/or K > 5 mmol/ml)

- Treatment with Angiotensin-Converting Enzyme (ACE) inhibitors or Angiotensin Receptor Blockers (ARB's)

- History of angioedema or other intolerance to ACE-inhibitors and ARB's. 

- Intolerance of intravenous contrast for MRI/CT.

- Aortic surgery within 6 months of inclusion

Eligible patients will be randomly assigned in a 1:1 ratio to receive losartan 2 × 50 mg or not. We will start with 50 mg and double the dosage to 100 mg after 14 days. The maximal tolerable dosage will be continued. Randomization is stratified according to site, with blocks of 10.

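### The renal exclusion is printed in the wrong units: the potassium limit cannot be met by any patient, and the creatinine limit is met only in extreme renal failure

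*Protocol article*

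**What the plan says.** The list under Exclusion criteria in the protocol article includes "Renal dysfunction (creatinine > 130 μg/ml and/or K > 5 mmol/ml". The two values are joined by and/or, so either one alone is meant to exclude a patient. They are the only laboratory entry limits the article prints.

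The same section then gives the treatment that patients who pass the screen may receive: "Eligible patients will be randomly assigned in a 1:1 ratio to receive losartan 2 × 50 mg or not". Dosing starts at 50 mg and is doubled to 100 mg after 14 days.

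No other section restates the two limits or gives them in other units. The Follow-up section lists blood samples at baseline without naming creatinine or potassium. The section on ethical aspects and trial organization says that an ethics committee approved the protocol, but that full protocol is not at hand.

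**The concern.** The criterion is labelled as renal dysfunction, yet the units attached to its numbers put both limits far outside anything that label describes. Followed literally, it would admit patients with serious renal impairment and with any degree of hyperkalaemia to a trial of an angiotensin receptor blocker.

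Two things are at stake. The first is safety screening, should the same text appear in a document that sites work from. The second is the description of the trial population: the article's entry limits tell readers to whom the results apply, and these limits cannot be taken at face value. Estimation and testing are not at stake.

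**Working it through.** **Inputs.** From Exclusion criteria: creatinine above 130 μg/ml and potassium above 5 mmol/ml. Not in the article, taken as physical constants: molar mass of creatinine 113.12 g/mol and of potassium 39.1 g/mol. The two main results (13 mg/dL and 5000 mmol/L) need neither constant. The article derives no figure from these limits, so there is no calculation of its own to reproduce; the check is unit conversion only.

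**Potassium as printed**
- 5 mmol/ml × 1000 ml/L = 5000 mmol/L.
- As mass: 5000 mmol/L × 39.1 mg/mmol = 195,500 mg/L, or 195.5 g of potassium per litre. This is physically impossible in a patient.

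**Creatinine as printed**
- 130 μg/ml × 100 ml/dL ÷ 1000 μg/mg = 13.0 mg/dL.
- In molar units: 130,000 μg/L ÷ 113.12 μg/μmol = 1149 μmol/L. This can occur, but only in extreme renal failure.

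**The presumed limits**
- Creatinine 130 μmol/L × 113.12 μg/μmol = 14,706 μg/L = 14.7 μg/ml = 1.47 mg/dL. Printed over presumed: 130 ÷ 14.7 = 8.8.
- Potassium 5 mmol/L. Printed over presumed: 5000 ÷ 5 = 1000.

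**Does one slip explain both?** No. For potassium, replacing ml by L is enough. The same replacement for creatinine gives 130 μg/L = 0.013 mg/dL, a limit so low that it would exclude everyone. The mass unit must change as well, from μg to μmol. The creatinine correction is therefore less mechanical than the potassium one, and should be confirmed from the source document.

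**Effect on the rest of the plan.** The sample size under Statistical considerations rests on a difference of 0.5 mm/year, a standard deviation of 1.5 mm, two-sided α of 0.05 and β of 0.2. Neither laboratory limit enters it, nor the planned covariate analysis.

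**The case against.** The strongest reply is that this is a misprint in a condensed article and nothing more. The ethics committee approved a protocol that is not shown and may well carry the right units. Nothing in the article links the printed units to what sites did. A clinician would reject the potassium unit on sight, and the criterion's own label shows its purpose. The 8.8-fold and 1000-fold figures compare thresholds and do not count patients: the article gives no distribution of creatinine or potassium in adults with Marfan syndrome, so the number falling between printed and presumed limits is unknown. Nor does the enrolment count (230 by October 2009) show that any patient was exposed to the error.

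Most of this stands, and it limits the weight of the point. No wrong enrolment is shown, the ratios must not be read as patients affected, and the enrolment figure adds nothing. It does not make the printed text right. An extraction fault is also unlikely: the two units are wrong in different ways on one line, and the μ has survived. The potassium limit corrects itself in the reader's mind; the creatinine limit does so less readily, because 13 mg/dL is a possible value and the repair changes two parts of the unit.

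**Conclusion.** The point holds. As printed, the potassium limb can exclude nobody and the creatinine limb excludes only patients at or above 13 mg/dL, so the criterion read literally excludes almost nobody. The conversions are exact apart from the two molar masses, which are used only for the μmol/L and gram figures. The 8.8-fold and 1000-fold excesses rest on the assumption that μmol/L and mmol/L were intended; the bare numbers fit those units, but the article does not state them.

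The point should be fixed because it concerns a stated safety-relevant threshold and costs almost nothing to correct. It does not bear on power, the type I error or the primary comparison, and it is no evidence of faulty conduct.

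**What to change.** Check both limits against the ethics-approved protocol and correct the printed line, presumably to creatinine above 130 μmol/L and/or potassium above 5 mmol/L. If the approved protocol is right, a one-line correction to the article is all that is needed.

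Only if the approved protocol or the case report form carries the same units is more required: correct those documents for the enrolment still to come, and review whatever baseline creatinine and potassium values exist for patients already enrolled. Whether such values were recorded cannot be told from the article.

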## Methods/Design

The COMPARE trial is an open-label, randomized, controlled trial with blinded end-points. Treatment with losartan will be compared with no additional treatment after 3 years of follow-up. We will enroll 330 patients with MFS who will be randomly assigned to receive losartan or not. Patients taking beta-blockers will continue taking their standard treatment. This multi-center study will be conducted in four academic centers in the Netherlands: Academic Medical Center in Amsterdam, University Medical Center St. Radboud in Nijmegen, University Medical Center Groningen and Leiden University Medical Center. A flow chart of the study design is shown in the Figure 1.

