### Objectives

#### Primary objective

The main objective of this study is to assess whether losartan reduces aortic dilatation at any aortic level, from the aortic root to the bifurcation. The primary end-point is the largest aortic diameter at any level measured by means of Magnetic Resonance Angiogram (MRA). If MRA is contraindicated, a Computed Tomography (CT) will be performed.

We will therefore test the null hypothesis that there is no significant difference in aortic diameters after 3 years of follow-up in the treated and the control groups. MRA's will be assessed by a person who is blinded for patient's treatment.

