## Ethical aspects and trial organization

The protocol has been approved by the Medical Ethical Committee of the Academic Medical Center in Amsterdam. The feasibility approvals have been obtained of all the participating centers. This trial is registered in the Netherlands Trial Register under number NTR1423. Enrollment began in March 2008 and in October 2009 230 patients have been enrolled.

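### One stated block length of 10 per site, with open treatment, makes up to one in six allocations certain in advance to a recruiter who knows the length and keeps a tally

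*Protocol article*

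**What the plan says.** The randomisation rule closes the Exclusion criteria section of the protocol article. "Eligible patients will be randomly assigned in a 1:1 ratio", and "Randomization is stratified according to site, with blocks of 10". No second block length and no random variation of length is mentioned.

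Methods/Design gives the setting. On masking it says: "The COMPARE trial is an open-label, randomized, controlled trial with blinded end-points". The control arm has no placebo, as the same section makes clear: "Treatment with losartan will be compared with no additional treatment after 3 years of follow-up". On the number of sites it says: "This multi-center study will be conducted in four academic centers in the Netherlands". Under Primary objective, blinding is confined to reading the scans: "MRA's will be assessed by a person who is blinded for patient's treatment".

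Ethical aspects and trial organization gives the state of recruitment: "Enrollment began in March 2008 and in October 2009 230 patients have been enrolled". The target is 330, so about 100 patients were still to come at that date.

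**The concern.** In a 1:1 block of 10, once one arm has received five patients, every remaining place belongs to the other arm. With no placebo, site staff see who received losartan. Because blocks run within site, a site needs only its own history to follow the sequence. Concealing the list centrally does not change this, since the information comes from past allocations that are visible.

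What is at stake is who enters each arm. The Background section describes routine monitoring of aortic growth as necessary, so a clinician may know how fast a patient's aorta has been growing before offering entry. The abstract states an expectation that losartan works. A clinician who shares it and can foresee the next allocation could bring forward or defer a patient accordingly. Steering fast growers towards losartan would hide a benefit; the reverse would exaggerate one. Blinded scan reading protects measurement, not entry. The covariate analysis under Statistical considerations names no earlier growth rate, and baseline diameter captures growth only in part.

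**Working it through.** The plan gives no figure for predictability, so there is none to reproduce.

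**Inputs.** Block length 10, ratio 1:1 (five per arm), stratified by site (randomisation paragraph); four sites, open treatment, untreated control and target 330 (Methods/Design); 230 enrolled by October 2009 (Ethical aspects and trial organization). Assumed, not stated: the length is constant, the recruiter knows it, and the recruiter sees the site's whole sequence.

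**Step 1: allocations known for certain.** There are C(10,5) = 252 equally likely blocks. The last k places are determined when they all belong to one arm, which has probability 2·C(10−k,5)/252.

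- k = 1: 252/252 = 100%
- k = 2: 112/252 = 44.4%
- k = 3: 42/252 = 16.7%
- k = 4: 12/252 = 4.8%
- k = 5: 2/252 = 0.8%

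The sum is 420/252 = 1.67 places per block, or 16.7%. This agrees with the closed form 2m/(m+1) for blocks of 2m: with m = 5, 10/6 = 1.67.

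**Step 2: number of patients.** 330 patients make 33 blocks: 33 × 1.667 = 55. For the 230 enrolled, 23 × 1.667 = 38; for 100 still to come, 10 × 1.667 = 17. These are expected counts under full knowledge at all four sites with complete blocks. They are therefore ceilings on what could be exploited on average, not estimates of what was.

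**Step 3: guessing without certainty.** Guess the arm that is behind, and toss a coin when the arms are level. Expected correct guesses per block are m + 2^(2m−1)/C(2m,m) − 0.5. For m = 5: 5 + 512/252 − 0.5 = 6.53, or 65.3%, against 50% by chance. This strategy needs only the running difference between arms, not the block length.

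**Step 4: what other block sizes would do.** The same formula gives these correct guesses per block: 2.83 (size 4), 4.10 (6), 5.33 (8), 6.53 (10), 7.72 (12), 8.89 (14). With each size used equally often:

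| Scheme | Correct guesses / places | Best-guess rate |
|---|---|---|
| 10 only | 6.53/10 | 65.3% |
| 4/6/8 | 12.26/18 | 68.1% |
| 8/10/12 | 19.58/30 | 65.3% |
| 10/12/14 | 23.14/36 | 64.3% |

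A shorter constant length is worse for certainty as well: with blocks of 4, 2m/(m+1) = 1.33 of 4, or 33%.

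**Step 5: possible size of bias (illustration only).** Suppose recruiters raise or lower expected growth by η according to the arm they foresee. Acting only on certain allocations shifts the difference between arms by 2 × 0.167η = 0.33η. Acting on every best guess shifts it by 2 × (2 × 0.653 − 1)η = 0.61η. The documents give no value for η. Taking 0.1 to 0.25 mm/year as an assumption, the shift runs from 0.03 to 0.15 mm/year, or about 7% to 31% of the 0.5 mm/year difference in the sample size calculation.

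**The case against.** Site-stratified permuted blocks are conventional, there are only four strata, and 10 is a fairly long block: it leaves half the certainty of blocks of 4 (16.7% against 33%). The sentence contradicts nothing else in the article. That a single constant length is used is inferred from one number in a condensed text. Who holds the list, whether sites know the length and who recruits are details that an article normally leaves to the full protocol. All of this stands, and it limits the priority of the point. It does not remove the point, because the length is a stated rule and predictability follows from it once treatment is visible.

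A reader might go further and infer that the length was published while patients were still being recruited, so that recruiters now know upcoming allocations. The documents do not support this. They give enrolment at October 2009 but no publication date. At the reported pace (230 over about 20 months, about 12 a month), the last 100 would take roughly 8 to 9 months, so recruitment may have been nearly or fully complete when the text appeared.

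A reader might also take 55 of 330 as a count of compromised allocations. It is a ceiling that requires a known length and a perfect tally at every site. Nor does undisclosed variation of block size cure the 65% guess rate, since guessing the arm that is behind works without knowing the length.

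**Conclusion.** The point holds as an avoidable weakness in a stated rule. One block length of 10 within site, combined with visible treatment, allows up to 16.7% of allocations to be known in advance: at most about 55 of 330, and at most about 17 of any 100 still to be enrolled. This rests on a constant length, known to recruiters, with the site's sequence tracked. The first is inferred from the single number given; the other two are not documented. The finding is one of opportunity, and nothing in the article shows that selection took place or that the treatment comparison is biased. Priority is optional to moderate: the exposure is limited and the remedy is cheap.

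**What to change.** **Patients still to be randomised.** Draw block sizes at random from a set of about 10 or longer, for example 10/12/14, and do not disclose the sizes to sites. The end of a block can then no longer be known for certain. The gain against simple guessing is small (65.3% to about 64.3%), so do not present the change as curing it. Avoid shorter blocks, constant or mixed. The cost is a new list and slightly more possible imbalance within a site: the largest imbalance from an unfinished block rises from 5 to 7.

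**Patients already enrolled.** Add a sensitivity check. With a losartan and b control allocations already made in the current block at that site, the next patient's probability of losartan is (5 − a)/(10 − a − b). For example, after three losartan and one control it is 2/6 = 0.33. Relate baseline aortic diameter, and earlier growth where known, to this probability, allowing for site. Without selection there should be no association. Position within block is the wrong variable: at position 10 the probability is always 0 or 1, equally often, so selection in opposite directions would cancel. The check needs only the randomisation list in order and baseline data. A null result would be reassuring but would not prove that selection was absent. If enrolment has closed, this check is the only part that still applies.

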### Follow-up

After inclusion the following will be obtained during the baseline investigations (V1):

• Patients medical history

• Echocardiography

• MRI or a CT of the heart and entire aorta

• Blood samples

• Punch skin biopsy

Patients will be evaluated after one, two and three years of treatment by means of echocardiography. After 4 weeks and one year of the treatment an additional skin biopsy will be obtained. At every visit, patient's medical history will be obtained. Date of dissection, operation or death will be carefully noted.

The final assessment will be after 3 years of treatment by means of MRI.

## Ethical aspects and trial organization

The protocol has been approved by the Medical Ethical Committee of the Academic Medical Center in Amsterdam. The feasibility approvals have been obtained of all the participating centers. This trial is registered in the Netherlands Trial Register under number NTR1423. Enrollment began in March 2008 and in October 2009 230 patients have been enrolled.

## Statistical considerations

Mean change in aortic diameter in patients with MFS is 0.9-1.5 mm/year[4]. Sample size calculation is based on the primary endpoint (rate of change of aortic diameter). The expected difference between two groups is 0.5 mm/year with a standard deviation of 1.5 mm (2-sided α = 0.05; β = 0.2). Based on these assumptions we calculated that 286 patients are required. To compensate for an estimated 20% drop-out, the inclusion of at least 330 patients is advised.

Primary analyses will be performed on an intention to treat basis. To evaluate the primary end-point a covariate analysis of the diameter change will be used in two groups (no treatment vs losartan) at baseline and after 3 years. Covariate analyses will be also used for the following secondary points: aortic volume, distensibility, pulse-wave velocity, left and right ventricle volumes. "Safety parameters" (i.e. mortality, dissections, surgery) will be evaluated by means of a X^2 ^test.

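### The enrolment of 330 covers about 13% drop-out, not the stated 20%; at 20% the unadjusted power is about 77% instead of 80%

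*Protocol article*

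**What the plan says.** The Statistical considerations section sizes the trial on the rate of change of aortic diameter. Its inputs are: "The expected difference between two groups is 0.5 mm/year with a standard deviation of 1.5 mm", with error rates given as "2-sided α = 0.05; β = 0.2". The result is: "Based on these assumptions we calculated that 286 patients are required". The next sentence adds the allowance for losses: "To compensate for an estimated 20% drop-out, the inclusion of at least 330 patients is advised".

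The Methods/Design section gives the same figure as the enrolment target: "We will enroll 330 patients with MFS who will be randomly assigned to receive losartan or not". The Abstract repeats it. Allocation is 1:1 (end of the Exclusion criteria section) and follow-up lasts 3 years.

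**The concern.** Two adjacent sentences give a required number, a drop-out rate and an enrolment figure, and the three do not fit together. If 286 evaluable patients are needed and a fifth of those enrolled are lost, 330 is too few. A reader who takes the paragraph at its word will believe that 80% power is protected against 20% drop-out, when the protection ends at about 13%. The trial's stated power and its stated tolerance for losses are therefore not both delivered by the stated size.

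A smaller matter sits in the same paragraph. The difference is given per year, but the standard deviation is printed in mm with no time unit, while the analysis concerns a change over 3 years. Anyone who later compares the planned with the observed standard deviation needs to know which quantity is meant.

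**Working it through.** **Inputs, all from Statistical considerations unless noted**
- Difference between groups: 0.5 mm/year
- Standard deviation: 1.5 (printed in mm), taken here as mm/year
- Two-sided α 0.05, power 80%
- Required: 286; drop-out: 20%; enrolment: 330
- Allocation 1:1 (Exclusion criteria section)

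**Step 1. Reproduce 286.** The standardised difference is 0.5/1.5 = 0.333.
- Normal approximation: n per arm = 2 × (1.960 + 0.842)² × (1.5/0.5)² ≈ 141.3, rounded up to 142, total 284.
- Two-sample t-test: 142.25 per arm, rounded up to 143, total **286**. Power with 143 per arm is 80.2%.

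The plan's 286 is therefore right on these inputs.

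**Step 2. Inflate for 20% drop-out.**
- Correct formula, N/(1 − d): 286/0.80 = 357.5, so **358**.
- Common shortcut, N × (1 + d): 286 × 1.20 = 343.2, so 344.
- Neither gives 330. The ratio used is 330/286 = 1.154.

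**Step 3. Drop-out that 330 tolerates.** 1 − 286/330 = 1 − 0.867 = **13.3%**.

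**Step 4. Evaluable patients and power at the plan's own 20%.**
- 330 × 0.80 = **264** (132 per arm), which is 286 − 264 = 22 short.
- Standard error of the difference: 1.5 × √(2/132) = 0.185 mm/year.
- Normal approximation: Φ(0.5/0.185 − 1.960) gives 77.3%. The t-test gives **77.0%**.
- Difference detectable with 80% power: (1.960 + 0.842) × 0.185 ≈ 0.517 mm/year, or 0.519 by the t-test, so about **0.52 mm/year**.

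**Power with 330 enrolled, by drop-out (t-test, unadjusted)**

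| Drop-out | Evaluable | Power |
|---|---|---|
| 0% | 330 | 85.5% |
| 10% | 297 | 81.7% |
| 13.3% | 286 | 80.2% |
| 15% | 280.5 | 79.4% |
| 20% | 264 | 77.0% |

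**Step 5. Unit of the standard deviation.** On the 3-year scale the difference is 3 × 0.5 = 1.5 mm.
- A standard deviation of 1.5 mm/year corresponds to 3 × 1.5 = 4.5 mm on that scale. The standardised difference stays at 0.333, and so does the 286.
- If 1.5 mm were instead the standard deviation of the 3-year change, the standardised difference would be 1.5/1.5 = 1 and the t-test would need only 17 per arm, 34 in total. The stated 286 rules this out.

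**The case against.** **The loss is small and conditional.** This stands. A reader might infer that the trial simply lacks 80% power. The document does not support that: with 330 enrolled, power is at or above 80% as long as drop-out stays at or below about 13%. At 20% the loss is 3 percentage points.

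**The text says at least 330, so 330 is only a minimum.** This helps little. Methods/Design and the Abstract give 330 as the planned number, and a minimum that fails at its own drop-out rate is still misstated.

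**The primary analysis uses covariates, whereas 286 comes from an unadjusted comparison.** This is a fair point. To make 264 patients as informative as 286, covariates would have to explain 1 − 264/286 = 7.7% of the variance, a correlation of about √0.077 = 0.28 with the outcome. That is an assumption: the article gives no correlation and takes no credit for one. The 77% should therefore be labelled as unadjusted.

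**Intention to treat keeps everyone in.** Only patients with a final measurement contribute one. The Follow-up section lists MRI or CT at baseline and MRI at 3 years, with echocardiography at the yearly visits. On that schedule a patient lost before year 3 has no follow-up value by the primary method.

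**The standard deviation is in the wrong unit.** A reader might infer this from the printed mm, and conclude that the sample size is wrong by a large factor. The document does not support it. The sizing endpoint is named as a rate of change, and 286 is reproduced exactly with 1.5 mm/year, so the calculation used matching units and the text has only left out the time unit. The alternative reading is excluded by the 286 itself; it would also remove the shortfall, since 264 patients would then give more than 99.9% power.

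**Conclusion.** The sentence on drop-out is wrong as written. No standard inflation takes 286 to 330 at 20%, and nothing else in the article explains the figure. The enrolment of 330 covers 13.3% drop-out. At the estimated 20%, 264 patients are evaluable, 22 too few, and power is about 77% (β about 0.23) instead of 80%.

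This rests on four assumptions: the standard deviation is 1.5 mm/year; the comparison is an unadjusted two-sample t-test; drop-out means that the final aortic measurement is missing; and losses are equal in the two arms. The article gives no source for the standard deviation, so its value cannot be checked here.

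The practical effect is modest. The required number of 286 is sound on its inputs, and the missing time unit on the standard deviation is a clarification, not an error in the calculation.

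**What to change.** Keep 330 and replace the drop-out sentence with wording such as:

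> A total of 330 patients gives 80% power with up to about 13% drop-out. With 20% drop-out (264 evaluable) power is about 77%, without credit for covariate adjustment.

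In the same paragraph, print the standard deviation as 1.5 mm/year (equivalent to 4.5 mm on the 3-year change), after confirming against the source that this is what was meant.

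Both changes are wording only. They need no extra patients and no change to the analysis; the stated power at 20% drop-out becomes slightly less favourable. If the sponsor prefers to keep the claim of 80% power at 20% drop-out, the target would have to be 358, which is 358 − 330 = 28 more patients.

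### Randomisation is stratified by site, but the test fixed for mortality, dissection and surgery ignores site; a site-stratified test is a minor improvement at no cost

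*Protocol article*

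**What the plan says.** **Allocation.** The Protocol article, Methods/Design, says: "This multi-center study will be conducted in four academic centers in the Netherlands". The randomisation paragraph at the end of Exclusion criteria adds "Eligible patients will be randomly assigned in a 1:1 ratio" and "Randomization is stratified according to site, with blocks of 10". Site is the only stratification factor named.

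**Events.** Secondary objectives combines death, new dissection and elective aortic surgery into one event endpoint. Statistical considerations treats these as safety parameters and names the test: "i.e. mortality, dissections, surgery) will be evaluated by means of a X^2 ^test". It does not mention site.

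**Primary endpoint.** Statistical considerations says: "To evaluate the primary end-point a covariate analysis of the diameter change will be used in two groups (no treatment vs losartan". The covariates are not listed.

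**Prosthesis.** Exclusion criteria rules out "More than one vascular prosthesis", so by implication a patient with one may enter. Prosthesis status is not a stratification factor.

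**The concern.** When allocation is balanced within sites, differences in event rate between sites cannot contribute much to the difference between arms. A pooled chi-square test still counts that between-site variation in its variance. If sites differ in event risk, for instance through case mix or referral for surgery, the pooled variance is too large for the design. The test then rejects less often than its nominal 5% under the null and has less power under an alternative.

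The stake is modest. The events are a secondary outcome, and the mismatch cannot produce a false claim of benefit more often than planned. It can only make a real difference in events slightly harder to see. For this outcome the test is named in the text, so the point does not depend on detail left to a document that is not shown.

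**Working it through.** **1. The plan's own figure.** The article gives no power calculation for the events. Its only sample-size figure, 286, concerns the primary endpoint: "The expected difference between two groups is 0.5 mm/year with a standard deviation of 1.5 mm", two-sided alpha 0.05, power 80%.

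- Normal approximation, per arm: 2 × (1.960 + 0.842)² × 1.5² / 0.5² = 2 × 7.85 × 9 = 141.3, rounded up to 142, so 284 in total.
- The t-test version gives 284.5 in total, or 143 per arm and 286 in total. The stated figure reproduces.
- It is an unadjusted two-sample calculation and has no bearing on the event test.

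**2. Inputs for the event test.** From the Protocol article: four sites, 1:1 allocation within site, 330 patients. Assumed, because the article gives none of these: site sizes of 150, 60, 60 and 60; the control event rates below; and a common odds ratio of 0.4 under the alternative.

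**3. Why the pooled test is conservative.** With N_k patients and event rate p_k at site k, and p the overall rate, under the null:

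- Variance per patient used by the pooled test: p(1 − p).
- Variance that applies when arms are balanced within site: Σ N_k p_k(1 − p_k) / 330.
- Approximate true size: two-sided tail area beyond 1.96 / √(ratio of the second to the first).

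*Equal rates, 10% at each site.* Both variances are 0.0900. The ratio is 1 and the size is 5.0%.

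*Rates 5, 10, 15 and 20%.*
- p = (7.5 + 6 + 9 + 12) / 330 = 0.1045, so p(1 − p) = 0.0936.
- Within-site variance: (7.125 + 5.4 + 7.65 + 9.6) / 330 = 0.0902.
- Ratio 0.964, square root 0.982, critical value 1.96 / 0.982 = 2.00, size about 4.6%.

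*Rates 2, 5, 10 and 30%.*
- p = (3 + 3 + 6 + 18) / 330 = 0.0909, so p(1 − p) = 0.0826.
- Within-site variance: (2.94 + 2.85 + 5.4 + 12.6) / 330 = 0.0721.
- Ratio 0.872, square root 0.934, critical value 1.96 / 0.934 = 2.10, size about 3.6%.

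**4. Simulation.** 20,000 trials per scenario compared the Pearson chi-square test with the Cochran-Mantel-Haenszel (CMH) test by site, both without continuity correction.

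| Control event rates across sites | Type I error, chi-square | Type I error, CMH | Power at OR 0.4, chi-square | Power at OR 0.4, CMH |
|---|---|---|---|---|
| 10% at all four | 5.2% | 5.0% | 53.2% | 53.2% |
| 5, 10, 15, 20% | 4.8% | 5.0% | 52.9% | 54.1% |
| 2, 5, 10, 30% | 3.9% | 5.1% | 42.9% | 47.5% |

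The Monte Carlo standard error is √(0.05 × 0.95 / 20,000) = 0.15 points for the error rates and at most √(0.25 / 20,000) = 0.35 points for each power. The 5.2% is therefore compatible with 5%. The pattern agrees with the approximation in step 3.

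**5. Reading the result.** The gain from stratifying the test is 0 points with equal rates, 54.1 − 52.9 = about 1 point with moderate differences, and 47.5 − 42.9 = about 5 points with extreme ones.

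**The case against.** The strongest reply is that nothing is wrong. The chi-square test keeps its type I error, the outcome is secondary, and the gain depends on site differences for which the article gives no evidence. In the two milder scenarios the gain is 0 to 1 point. All of that stands. It is why this is an improvement and not an error.

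A reader might also infer something larger: that the primary analysis is a bare two-group comparison, that leaving out site and prior prosthesis makes its standard error 3-10% too large, and that adjustment would lift power from 77% to 80-85% with 264 patients (330 less 20%). The document does not support this, for four reasons.

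- The text specifies a covariate analysis. The mention of two groups names the arms being compared. An article that condenses a full protocol commonly leaves the covariate list to it, so an unlisted covariate is not an omitted one.
- Prosthesis is not a stratification factor, so the design gives no reason of its own to adjust for it. It is a candidate prognostic covariate. One replaced segment does not by itself imply a smaller maximum change over the remaining native aorta.
- The larger figures need a between-site SD of 0.3-0.5 mm/year (0.3²/2.25 = 4.0% to 0.5²/2.25 = 11.1% of variance). The expected range across four sites is about 2.06 SD, so 0.6-1.0 mm/year. The whole range of mean growth quoted in Statistical considerations, 0.9-1.5 mm/year, is only 0.6 wide. The prosthesis share (20-30%) and growth gap (0.6-0.9 mm/year) behind those figures have no source in the document either.
- If the factors explain only 1-2% of variance, power with 264 patients moves from 77.3% to 77.7-78.1%.

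The shortfall of 264 against 286 is a separate matter of drop-out arithmetic and adds no weight here.

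**Conclusion.** The point holds for the event comparison only. Allocation is stratified by site, and the test named for mortality, dissections and surgery does not use site. The test is valid, and slightly conservative if event rates differ between the four centres: simulated type I error was 3.9% at the extreme and about 5% otherwise. A site-stratified test gains between nil and about 5 points of power and lost none in the scenarios examined. These sizes rest on assumed event rates, site sizes and an odds ratio of 0.4.

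For the primary endpoint, no omission of site or prosthesis is shown, and neither a 3-10% excess in the standard error nor a rise in power to 80-85% is established. Including site there would be consistent with the stratified design, but the text does not contradict it. The point is minor.

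**What to change.** In Statistical considerations, replace the plain chi-square test for the events with a Cochran-Mantel-Haenszel test stratified by site (four strata), reported with the common odds ratio and its confidence interval. Record the change before the 3-year data are read.

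Optionally, in the same edit, state that site is among the covariates of the primary analysis, or point to the document that lists them.

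The cost is wording only. Site is known for every patient from randomisation, and neither data collection nor sample size changes.
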